#### Analyses of secondary outcomes

Competing-risk proportional hazards survival models will be used to analyse time-to-event outcomes during patient hospitalisations (outcomes 2, 4, 5, 6 and 7). Hospital discharge and in-hospital deaths are treated as competing risks. Use of the competing risk survival model provides an estimate of the intervention effect which appropriately accounts for the competing and time-varying nature of discharge and death on the outcomes [41]. The models will have a binary variable indicating if patients were in the intervention exposure phase. The survival analysis will adjust for likely predictors of patient age, sex and time spent in hospital for identified hospital episode prior to admission to enrolled clinical team. The survival analysis will stratify by clinical teams to control for consistent differences between teams. Cumulative incidence curves will be used to compare the event rates over time between the usual care exposure and intervention exposure phases.

We will use a proportional hazards survival model to investigate the difference between usual care and intervention exposure phases in the time to re-admission within the first 12 weeks after index discharge (outcome 3). Patients who died after leaving hospital or were not re-admitted within the 12 weeks will be censored. Clinical teams will be included as strata.

Data on the health services used by patients during their hospital admission will be retrieved from the hospitals’ clinical costing database to evaluate changes in admission and treatment costs (outcome 8). Any costs that occurred before the patient was identified to be in the at-risk population will be excluded. Statistical distributions will be fitted to describe variability in all cost parameters. The key measure of cost will be the average cost per patient. This will be presented alongside 95% bootstrap confidence intervals to estimate the uncertainty in this average.

The costs of implementing the intervention (outcome 9) will be measured by the staff time associated with collecting, interpreting and providing the feedback, and for all activities required to establish the intervention. The economic opportunity costs of healthcare workers’ time will be valued by Queensland Health wage rates. Quantities and types of consumables and incidentals used will be valued in dollar terms by market price. The outcome will be reported as the estimated total cost of the intervention and bootstrapped 95% confidence interval.

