#### Statistical analyses

We will use R for data management, modelling and graphics [33]. We will make all our R code publicly available via GitHub. We will use EQUATOR guidelines to write-up our results, using the CONSORT guidelines for randomised trials, the extension for stepped-wedge trials [39, 40]. Additional details of the statistical analysis plan are provided online [37].

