#### Analysis of primary outcome

The primary outcome, proportion of patients with at least one ICU admission, will be analysed using a mixed effects Binomial regression. The key variable is the timing of the switch from usual care exposure to intervention exposure phase. The intervention timing regression coefficient will be treated as a random slopes term to account for potential differences in intervention effects across clinical teams. A linear time covariate will be included to capture a potential calendar time trend. The model will also adjust for likely predictors of patient age and sex. The model will include a random intercept for each enrolled clinical team to account for any underlying differences in the proportion of patients with ICU admissions between the teams.

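### As printed, the re-admission model (Outcome 3) lists team strata but no patient covariates, although the plan adjusts its other six impact outcomes for age and sex; add them

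*Protocol article*

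**What the plan says.** The section Analyses of secondary outcomes treats the survival outcomes in two separate paragraphs.

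The first covers "time-to-event outcomes during patient hospitalisations (outcomes 2, 4, 5, 6 and 7" and uses competing-risk models. Its adjustment sentence reads "The survival analysis will adjust for likely predictors of patient age, sex and time spent in hospital for identified hospital episode prior to admission" to the enrolled team, and the next sentence adds stratification by clinical team.

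The second covers Outcome 3 alone: "We will use a proportional hazards survival model to investigate the difference between usual care and intervention exposure phases in the time to re-admission" over the 12 weeks after index discharge. It then gives the censoring rule, "Patients who died after leaving hospital or were not re-admitted within the 12 weeks will be censored", and ends with "Clinical teams will be included as strata". No patient covariate appears.

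For the primary outcome, the section Analysis of primary outcome says "The model will also adjust for likely predictors of patient age and sex" and also includes a linear calendar-time term.

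**The concern.** The plan itself names age and sex as likely predictors and uses them for every impact outcome except re-admission. The design gives a reason to want them there too. What is randomised is when each hospital switches, not which patients receive the intervention, and the Discussion says that all teams at a site cross over together. In a model stratified by team, every comparison is made inside one team. No team has usual-care and intervention patients in the same calendar period, so the phase hazard ratio rests on earlier versus later patients of the same team.

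Strata remove stable differences between teams. They do nothing about a team's later patients being older, or differently mixed by sex, than its earlier ones. If that happened and age or sex predicts re-admission, part of the difference would be read as an intervention effect.

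Outcome 3 has one further exposure. It is timed from discharge, so it is observed only in patients who leave hospital alive, and discharge alive versus death is itself part of Outcome 2. The patients at risk of re-admission could therefore differ between phases even without drift in admissions. Adjusting for age and sex would reduce that only in part.

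**Working it through.** **Step 1. Model terms side by side (Protocol article, the two analysis sections).**

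| Outcome | Model | Patient covariates listed | Handling of teams |
|---|---|---|---|
| 1 (primary) | Mixed effects binomial | Age, sex | Random intercept, random intervention slope |
| 2, 4, 5, 6, 7 | Competing-risk proportional hazards | Age, sex, prior time in hospital | Strata |
| 3 | Proportional hazards | None listed | Strata |

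Age and sex are listed for six of the seven impact outcomes; Outcome 3 is the exception.

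**Step 2. Could the adjustment sentence in the first paragraph carry over to Outcome 3?** It speaks of the survival analysis in general terms, so the reading is possible. However, the stratification sentence that follows it has the same general subject. If both carried over, there would be no need to restate strata for Outcome 3. The strata are restated and the covariates are not. The more natural reading is that the Outcome 3 paragraph is complete in itself and has strata only.

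**Step 3. Size.** The article gives no figure to reproduce: no re-admission rate, no hazard ratio for age or sex, and no case-mix comparison between phases. The stated power (95%, or 79.3% at a within-ward correlation of 0.01) concerns ICU admission only. All inputs below are therefore assumed, and the formulas are first-order approximations.

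*Age.* Factor on the phase hazard ratio = (hazard ratio per year)^(difference in mean age between phases).

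| Hazard ratio per year | 0.5 years | 1 year | 2 years |
|---|---|---|---|
| 1.00 | 1.000 | 1.000 | 1.000 |
| 1.01 | 1.005 | 1.010 | 1.020 |
| 1.02 | 1.010 | 1.020 | 1.040 |
| 1.03 | 1.015 | 1.030 | 1.061 |

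The largest entry is 1.03^2 = 1.061.

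*Sex.* With hazard ratio h for the higher-risk sex, its share p = 0.5 in one phase and p + s in the other, factor = [1 + (p + s)(h − 1)] / [1 + p(h − 1)].

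| h | s = 0.02 | s = 0.05 | s = 0.10 |
|---|---|---|---|
| 1.1 | 1.002 | 1.005 | 1.010 |
| 1.2 | 1.004 | 1.009 | 1.018 |
| 1.3 | 1.005 | 1.013 | 1.026 |

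The largest entry is (1 + 0.60 × 0.3) / (1 + 0.50 × 0.3) = 1.18 / 1.15 = 1.026.

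A shift in the opposite direction moves the hazard ratio the other way by a similar amount; for age, 1 / 1.061 = 0.943. The range is thus 0% to about 6% for age and under 3% for sex, in either direction.

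**The case against.** The strongest reply is that silence in a condensed article is not a decision. The Outcome 3 paragraph never says that the model is unadjusted. The article was adapted from a fuller protocol, and the section Statistical analyses says "Additional details of the statistical analysis plan are provided online [37". A covariate list for one secondary outcome could well be there. This stands to the extent that a reader might infer that the investigators chose an unadjusted analysis, and the text does not establish that. It does not dispose of the point. The article did print covariates for the other six impact outcomes and then gave Outcome 3 its own specification without them, so the printed specifications differ from one another.

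A reader might also infer that the re-admission hazard ratio will be biased. The documents do not support that. They show no case-mix shift, the same age and risk-score criteria define the at-risk population in both phases, and the fair range of the effect starts at zero.

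Nor should lost precision be claimed as a cost. In a proportional hazards model, adding prognostic covariates does not generally shrink the standard error of the log hazard ratio. Any gain is mainly in power, because the conditional estimate tends to lie further from the null.

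Finally, age and sex would not remove a calendar trend, and prior time in hospital has a more obvious role in models of in-hospital timing than in re-admission after discharge. Both remarks are correct and limit what the fix should claim.

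**Conclusion.** The point holds as a minor inconsistency in how one secondary outcome is specified. Read as printed, the re-admission model contains the phase contrast and team strata only, so a change in age or sex mix between a team's earlier and later patients would not be adjusted for. Whether such a change will occur is unknown. If mean age differs by 0.5 to 2 years with a hazard ratio of 1.00 to 1.03 per year, the phase hazard ratio moves by 0% to about 6%. If the sex mix differs by 2 to 10 percentage points with a hazard ratio of 1.1 to 1.3, it moves by under 3%. These inputs are assumptions, not figures from the trial. The primary outcome is unaffected.

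**What to change.** Add patient age and sex to the Outcome 3 proportional hazards model, keeping team strata. For prior time in hospital, either include it so that the survival models match, or state in a sentence why it is left out for an outcome that starts at discharge. If the online analysis plan already lists these covariates, bring the article's wording into line with it.

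The cost is one line of model code and one sentence of text. The plan already uses these variables for the same at-risk patients in the other models, so no new data are needed. Fixing the covariates before the analysis also removes a later choice between adjusted and unadjusted results. The text should claim no more than adjustment for measured case mix: a calendar trend in re-admission would need separate handling.

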**Health care resource use and cost outcomes**		
Outcome 8	Changes in admission/hospitalisation and treatment costs	Costs of treatment will be taken from routinely collected information and will begin accumulating from the date first recorded as *high-risk CriSTAL and SPICT positive*. This ensures that treatment costs reflect only those costs that relate to care provided at the end-of-life phase. All costs will be stratified by the acute and palliative care phases so that any changes resulting from different treatment pathways can be identified.
Outcome 9	Cost of implementing the prospective feedback loop intervention	The cost of implementing the study intervention will be measured by the duration and unit costs of staff time associated with completing direct trial activities (including document review and clinical team feedback activities).

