## Discussion

The emphasis of this study is to support clinicians to recognise the potential for non-beneficial treatment at the end of life using a feedback loop that relays objective information about risk profiles in relation to death and deterioration. The tailored clinical response promotes communication, engagement and awareness. Audit and peer feedback approaches have been considered promising for over two decades in areas such as improving the accuracy of clinical documentation [44] and potentially assisting in clinician’s behaviour change [45].

The expected benefits are improved patient outcomes in terms of reduction in non-beneficial treatments following the clinical team response to the patient record review data, specifically the CriSTAL and SPICT scores and indicators. This should facilitate planning and delivering appropriate care and treatment to those patient groups. Cost savings may be observed due to the prevention of non-beneficial treatments. In addition, the qualitative process evaluation will identify key factors to the intervention’s implementation and performance, as well as the potential to be implemented at other hospitals, in line with best-practice recommendations for these interventional trials [30, 46].

The stepped-wedge design used has several strengths. The incremental roll-out of the stepped-wedge design is practical to implement, mimics how the intervention might be implemented in practice at other hospitals [47] and is well-suited to the evaluation of health service delivery interventions [43]. This design allows the study team to work with each hospital during the intervention establishment phase. Each hospital contributes data to both the control and intervention conditions, mitigating risk associated with comparing heterogeneous hospitals. This crossover also means that temporal effects can be studied [48] with more efficiency than other cluster designs [49]. The risk of contamination between sites and teams is minimised by geographical separation of sites and simultaneous crossover of clinical teams within the same site. The main drawbacks of this design are the potential risk of secular trends unrelated to the intervention exposure, and risk of unequal exposure to seasonal trends. These risks were taken into consideration in the statistical analysis plan.

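### Outcome 8 is a change in cost, but its key measure and bootstrap interval are for the average cost per patient, and no between-phase contrast is specified

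*Protocol article*

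**What the plan says.** Table 1 names Outcome 8 "Changes in admission/hospitalisation and treatment costs" and starts cost accrual on the date a patient is first recorded as at risk on both tools. The one stratification it mentions concerns type of care: "All costs will be stratified by the acute and palliative care phases".

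Under Analyses of secondary outcomes, the article says that clinical costing data will serve to evaluate changes in cost and that distributions will be fitted to the cost parameters. It then fixes the summary: "The key measure of cost will be the average cost per patient. This will be presented alongside 95% bootstrap confidence intervals". The second of these sentences, in full, fixes what the interval covers: "This will be presented alongside 95% bootstrap confidence intervals to estimate the uncertainty in this average".

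On the design, the Randomisation section says that all three hospitals receive the intervention at randomised times. The Discussion describes "simultaneous crossover of clinical teams within the same site" and gives this as a strength: "Each hospital contributes data to both the control and intervention conditions, mitigating risk associated with comparing heterogeneous hospitals".

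**The concern.** An average with its interval says how well a cost level is known. It does not say whether cost changed when the intervention began, which is what Outcome 8 asks. A reader of the results would have to form the comparison from averages the plan never sets against each other.

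The design makes the form of that comparison important. A hospital that crosses early contributes relatively more intervention patients, and one that crosses late relatively more usual-care patients. If hospitals or teams differ in mean cost, plain averages for the two phases differ even when no team's cost has moved. Intervention patients are also seen later on average, so any drift in cost over the trial enters the comparison as well.

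At stake is the cost conclusion. The article lists change in health service use and costs within its first objective and anticipates savings in the Discussion. A saving or an excess could reflect the order in which the hospitals were drawn.

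**Working it through.** The article gives no cost mean, standard deviation or difference, so there is no figure to reproduce. The check has three parts.

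**1. What is stated for each outcome**

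| Outcome | Contrast named | Team handling | Calendar time |
|---|---|---|---|
| 1 (ICU admission) | switch from usual care to intervention | random intercept, random slope | linear term |
| 2, 4, 5, 6, 7 (in-hospital times) | binary phase indicator | strata | none named |
| 3 (re-admission) | usual care against intervention | strata | none named |
| 8 (cost) | none; average cost per patient | none named | none named |

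The article sets out the contrast and team handling for the other patient outcomes. For cost it states a different target.

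**2. Hospital mix with zero true change**

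Formula: phase mean = sum over hospitals of (hospital's share of that phase's patients × hospital mean cost).

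From the article: 3 hospitals, 7 teams each, and 3 at-risk patients per team per week, so 7 × 3 = 21 patients per hospital per week. Assumed: weeks of usual care/intervention per hospital, in order of crossover, and relative hospital mean costs in the same order.

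- Layout A: 15/35, 25/25, 35/15
- Layout B: 10/30, 20/20, 30/10
- Layout C: 13/26, 26/26, 39/13

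Worked case, layout A with costs 1.0, 1.1, 1.2:

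- Usual care: (15×1.0 + 25×1.1 + 35×1.2)/75 = 84.5/75 = 1.127
- Intervention: (35×1.0 + 25×1.1 + 15×1.2)/75 = 80.5/75 = 1.073
- Apparent change: 1.073/1.127 − 1 = −4.7%

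| Relative hospital costs | A | B | C |
|---|---|---|---|
| 1.0, 1.0, 1.0 | 0% | 0% | 0% |
| 1.0, 1.1, 1.2 | −4.7% | −5.9% | −4.7% |
| 1.2, 1.1, 1.0 | +5.0% | +6.2% | +5.0% |
| 1.0, 1.2, 1.4 | −8.5% | −10.5% | −8.4% |
| 1.0, 1.25, 1.5 | −10.1% | −12.5% | −10.0% |

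In every cell the within-hospital change is 0. The sign depends only on whether the cheaper hospital crosses first.

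For scale, assume a patient cost CV of 1.5 and independent patients. Layout A has 21 × 75 = 1,575 patients per phase. With equal hospital costs, the 95% half-width of the difference is 1.96 × 1.5 × √(2/1,575) = 0.105, about 10% of the mean. Recomputed at each cost spread, on a base hospital cost of 10,000, the spurious difference in layout A is 533 against a half-width of 1,153 (ratio 0.46) at spread 1.0–1.2, and 1,333 against 1,311 (ratio 1.02) at 1.0–1.5.

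**3. Calendar time**

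Take layout A with an assumed 5-week establishment gap, weeks numbered from 0.

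- Mean week of usual-care patients: (15×7 + 25×12 + 35×17)/75 = 13.3
- Mean week of intervention patients: (35×37 + 25×42 + 15×47)/75 = 40.7

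The plain comparison therefore spans 27.3 weeks of drift. Within each hospital the gap is 37−7 = 42−12 = 47−17 = 30 weeks. Each 1% of annual cost drift adds about 27.3/52 = 0.53% to the plain comparison and 30/52 = 0.58% to a within-team one without a time term. A within-team contrast removes the mix effect but not the trend.

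**The case against.** The strongest reply is that the article is a condensed account. It says outright that changes in cost will be evaluated, so a comparison is intended. It refers to an online analysis plan for further detail, and covariates, clustering and the resampling unit are matters an article may leave there. The sentence about fitting distributions suggests more modelling than two raw means.

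Much of this stands, and it limits the point. A reader might infer that costs will be averaged over all hospitals together. The text does not say so; it is silent on whether averages are formed overall, by study phase, by hospital or by team. A reader might also infer that no interval for the change will ever be produced. The article specifies none, but the online plan may. A third tempting inference is that change will be judged by whether two separate intervals overlap, with a loss of power. The article describes no such rule, so that argument has no place here. The fitted distributions are said to describe variability in the cost parameters; they are not tied to a contrast.

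The reply does not remove the mismatch in what is stated. The article names the key measure and says what its interval covers, and both describe a level while the outcome is a change. An online plan with an adjusted difference as the key measure would differ from the article on this point, and the two would still need to be reconciled.

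**Conclusion.** The point holds in this form: the measure and interval fixed for Outcome 8 do not match the outcome, and no contrast that accounts for team, hospital or calendar time is specified. This is a stated choice that should be corrected. It concerns a secondary outcome and does not touch the primary analysis or the power figures.

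Bias from hospital mix is conditional. It arises if plain phase averages are compared and mean costs differ between hospitals or teams; with equal costs it is zero. Under the three assumed layouts it is about 5% to 6% in either direction at a hospital cost spread of 1.0–1.2, and about 10% to 12.5% at 1.0–1.5. At a CV of 1.5 that is from roughly half of the 95% half-width to slightly more than all of it. The layouts, cost spreads, CV and gap are illustrative assumptions, not facts about this trial.

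**What to change.** Make the key measure of Outcome 8 the difference in mean cost per patient between intervention and usual-care exposure. Estimate it from a model with clinical-team effects, a linear calendar-time term, age and sex, for example a gamma model with log link, taking the difference from predicted mean costs under each phase. Team effects also absorb differences between hospitals, because teams are nested in hospitals. The time term mirrors the primary analysis and is needed in a one-way crossover.

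Give a 95% bootstrap interval for that difference, resampling whole teams within hospital and keeping both phases of a team together. Resampling hospitals would be unreliable with only three. Keep the phase averages, and the acute/palliative split, as descriptive figures. If the online analysis plan already specifies a contrast, align the two texts.

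The cost is a change of wording and a little more analysis code, with no new data. The interval for the change will probably be wider than one from resampling individual patients.

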#### Process evaluation data analysis

Interview notes and transcripts, and monitoring and field records will be entered into NVivo [42] and analysed qualitatively. The CFIR framework constructs – intervention characteristics, individual characteristics, inner setting, outer setting and process – will be used as an initial coding framework for the data [35]. Within these broad constructs, thematic analysis will be used to identify and compare patterns in the data within and across intervention sites [43]. Data that are distinct from the CFIR constructs will be analysed inductively, again using a thematic approach. Coding and cross-checking of data will be undertaken independently by two research team members. Differences will be discussed and, where necessary, additional members of the research team will be engaged to reach agreement. Analyses will be synthesised to produce a narrative account of the processes of implementation in relation to observed outcomes.

